## 2.5 Compliance with various standards

This study will be conducted in compliance with this study protocol, the standards stipulated in Article 14, Clause 3 and Article 80-2 of the Pharmaceutical Affairs Law, the “Contents of the Good Clinical Practice (GCP) (Report of the Central Pharmaceutical Affairs Council)” (hereinafter referred to as Report GCP) dated March 13, 1997, Ordinance No. 28 of the Ministry of Health and Welfare dated March 27, 1997 “Ordinance on Good Clinical Practice” (Ordinance GCP), and *Yakuhatsu* No. 430 dated March 27, 1997 “Enforcement of the Ordinance on Good Clinical Practice,” Ordinance No. 172 of the Ministry of Health, Labour and Welfare dated December 21, 2004 “Ordinance for Partially Revising the Ordinance on Good Clinical Practice,” the Declaration of Helsinki, and the study contract signed by the sponsor and the study center.

# 3. Study objectives

This 8-week repeated administration study compares the NIK-333 doses of 300 mg/day and 600 mg/day in patients who were completely cured of hepatitis C virus (HCV)-positive HCC by examining the changes in liver and peripheral gene expression profiles before and after administration of each dose and the drug concentrations in the liver and plasma. After the above test (liver biopsy), NIK-333 of 600 mg/day is administered to all subjects until Week 96 (88 weeks) to investigate safety, with a focus on the cardiovascular system, and the changes of plasma drug concentrations during long-term administration.

# 4. Study design

## 4.1 Study design

(1) Type of study

Step I: Open-label, randomized, parallel-group, comparison study in which NIK-333 is administered repeatedly at the dose of 300 mg/day or 600 mg/day (Week 0 to Week 8)

Step II: Open-label study in which NIK-333 is administered at 600 mg/day alone (Week 8 to Week 96)

(2) Flow chart of the study design, procedure and steps

Follow-up examination

Subject selection period

Study drug administration period

Step I

Step II

| Radical therapy  0  Gene expression profile  Pharmacokinetics in liver and peripheral blood  Safety evaluation  Pharmacokinetics in plasma  8  Week 12 after  completion of  administration  Week 96 |  | Briefing/Informed consent |  | Confirmation of complete cure |  | Registration |  |  | |
| --- | --- | --- | --- | --- | --- | --- | --- | --- | --- |
| Administration of 300 mg/day |  |
|  | |
| Administration of 600 mg/day | Administration of 600 mg/day |
|  | |

(3) Target sample size

12 subjects

Subjects will be divided into the following two groups in Step I (Week 0 to Week 8).

NIK-333 300-mg group: 6 subjects

NIK-333 600-mg group: 6 subjects

All subjects will receive 600 mg/day in Step II (Week 8 to Week 96).

## 4.2 Evaluation parameters

[1] Gene expression profile

Liver and peripheral blood gene expression profiles determined by the microarray method

[2] Safety

Adverse events, physiological tests, laboratory tests (hematology tests, blood biochemistry tests, urinalysis, blood pressure parameters), abdominal imaging diagnosis, endoscopy (esophagus/stomach), bone mineral analysis (DXA method), ECG, echocardiography, pulse wave examination (PWV/ABI), fundus examination

[3] Pharmacokinetics (unchanged NIK-333 and NIK-333 lipids form)

1) Drug concentrations in the liver: Concentrations of unchanged NIK-333 and NIK-333 lipids form

2) Drug concentrations in plasma: Concentrations of unchanged NIK-333, NIK-333 lipids form and NIK-333 metabolite

3) Drug concentration in urine: Unchanged NIK-333

[4] Exploratory biomarker

TGF- concentration in plasma (biomarker related to gene expression)

## 4.3 Blinding procedures and maintenance of blindness

No blinding procedures are conducted in this study.

## 4.4 Administration method, doses and administration period

(1) Administration method

Orally administer the designated dose twice daily, after breakfast and after supper.

[Rationale]

Administration after meals was selected because: the results of the phase I clinical studies showed no significant differences in plasma concentration of unchanged NIK-333 between the fed and fasted conditions; good compliance is expected for administration after meals in clinical settings; and there are no reasons why administration in the fasted condition should be strongly recommended.

(2) Doses

NIK-333 of 300 mg (2 capsules x twice/day) or 600 mg (4 capsules x twice/day) (One capsule contains 75 mg of NIK-333.)

[Rationale for the doses]

Muto et al. administered to patients who had received treatment for HCC a substance identical to NIK-333 at the dose of 600 mg/day (twice daily) for 1 year, and found that the substance had an inhibiting effect on recurrence of HCC.13) On the basis of these findings, a single administration study of 3 doses (600 mg/day as the main dose and 300 and 900 mg/day) and a 48-week repeated administration study were conducted as phase I clinical studies to confirm the pharmacokinetics and tolerability of NIK-333. As a result, unchanged NIK-333 was confirmed to exhibit linear pharmacokinetics in the dose ranging from 300 to 900 mg/day. With regard to tolerability in the repeated administration study, blood pressure increase was observed as an adverse drug reaction at the dose of 900 mg/day (twice daily), but no serious and significant adverse drug reactions were seen at 300 and 600 mg/day (twice daily).

In the pharmacology studies, on the other hand, NIK-333 administered at the dose of 40 mg/kg was confirmed to significantly inhibit chemical carcinogenesis induced by 3'-MeDAB and DEN15) in rat liver. The peak plasma concentration of unchanged NIK-333 after single administration of 40 mg/kg (effective dose) in rats was 0.5 µM (151 ng/mL). Since the liver/plasma concentration ratio after single oral administration in rats is 2 to 6, the concentration of unchanged NIK-333 in liver tissues is estimated to be 1 to 3 µM. Therefore, after a dose of 40 mg/kg, the NIK-333 concentration in liver tissues was assumed and confirmed by *in vitro* studies to have reached the IC50 for the cell growth-inhibiting action (0.220 µM, 66.5 ng/mL), the EC50 for the differentiation-inducing action (4.3 µM, 1300 ng/mL), and the IC50 for the apoptosis-inducing action (1.91 µM, 578 ng/mL).

In the phase I clinical study, the peak concentrations of unchanged NIK-333 after single administration of 300, 600 and 900 mg were 1.0 µM (316.1 ± 275.9 ng/mL), 1.5 µM (468.4 ± 191.0 ng/mL) and 3.0 µM (906.9 ± 579.6 ng/mL), respectively. From these results, the concentrations in human liver tissues at each dose (twice daily) are calculated to be 1.0 to 3.1 µM (316.1 to 948.3 ng/mL), 1.5 to 4.6 µM (468.0 to 1404.0 ng/mL) and 3.0 to 9.0 µM (907.0 to 2721.0 ng/mL), respectively, suggesting that the concentrations which are confirmed to be effective in *in vitro* studies have already been reached after administration of 300 mg/day. In other words, judging from the concentrations of unchanged NIK-333 in plasma and liver tissues obtained from the effective dose in the pharmacology studies, the dose of 300 mg/day (twice daily) is expected to be effective based on comparison between rats and humans. The dose of 600 mg/day (twice daily) is equivalent to a twice-daily administration of 100 mg/kg in rats in terms of the blood concentration, and may be regarded as an excessive dose from the point of view of pharmacokinetics.

For these reasons, we have decided to determine the gene expression profile of liver, and peripheral blood and drug concentrations in the liver and plasma before and after 8-week repeated administration of the following two doses: 300 mg/day (twice daily) of which efficacy can be expected from the blood concentration, and 600 mg/day (twice daily) which has been confirmed to be effective by Muto et al., and which has also been confirmed to be tolerable during 48-week administration in phase I clinical studies (Step I). If the liver biopsy scheduled on the day of evaluation at Week 8 is postponed in Step I, the period of Step I will be extended until completion of liver biopsy. In other words, the period of administration of two doses, i.e., 300 mg/day (twice daily) and 600 mg/day (twice daily) will also be extended. After completion of the above test (liver biopsy), all subjects will receive 600 mg/day (twice daily) of NIK-333 until Week 96, and the safety and the time course of drug concentration in plasma during long-term repeated administration at a high dose will be examined (Step II).

(3) Study drug administration period

96 weeks (Step I; Week 0 to Week 8, Step II; Week 8 to Week 96)

[Rationale]

Step I:

The administration period for determination of the gene expression profile was selected with an intention to determine the best possible timing for identifying expressions of the genes that quickly respond to the drug after the start of NIK-333 administration, while taking into consideration the physical burden of liver biopsy on the patients and feasibility of administration at the study center. Since the results of examination of pharmacokinetics in the phase I repeated administration study of NIK-333 showed that a steady state was reached at Week 2 of repeated administration, the study drug administration for at least two weeks was considered necessary for determination of the gene expression profile. Also considering the stress imposed on the liver by the two liver biopsies, the administration period for determination of the gene expression profile was set at 8 weeks.

Step II:

The experience of long-term administration of the study drug is confined to the clinical study conducted by Muto et al.13) and the phase I study. The reports by Muto et al. suggest that the effect of 1-year administration tends to be maintained for a long period. However, due to the small sample size, it has not confirmed whether adequate clinical effects are maintained long during 1-year administration. Therefore, the administration period has been set at 96 weeks in the phase II/III study of NIK-333 to examine the changes in the recurrence-inhibiting effect of repeated administration of the study drug. Thus, the optimal administration period will be evaluated based on the comparison between the inhibitory effect after completion of administration and the preceding inhibitory effect. However, while the safety of NIK-333 in administration for up to one year has been confirmed in the phase I study, safety in long-term administration for more than one year has not been investigated to date. In particular, in view of the blood pressure-increasing effect observed at 900 mg/day, the safety and pharmacokinetics of NIK-333 of 600 mg/day in administration for up to 96 weeks will be investigated by examining the cardiovascular and urinary systems.

## 4.5 Follow-up examination

(1) Follow-up examination of safety

Conduct medical examination, determination of vital signs, abdominal imaging diagnosis, determination of tumor markers, and laboratory tests at Week 12 after completion of the study drug administration.

[Rationale]

Conduct tests to ensure the subjects’ safety after completion of the study drug administration.

(2) Follow-up examination of pharmacokinetics

Determine drug concentrations in plasma at Week 12 after completion of the study drug administration.

[Rationale]

To confirm elimination of the study drug from plasma after repeated administration of NIK-333

(3) Other follow-up examinations

If any other abnormal findings (adverse events or abnormal laboratory values) are observed, conduct follow-up examinations as needed.

## 4.6 Expected period of subjects’ participation

The expected period of subjects’ participation is equivalent to the study drug administration period (96 weeks).

## 4.7 Amount of liver tissue samples collected and frequency of sample collection

Perform liver biopsy and collect liver tissues on the day before the start of study drug administration and at Week 8 of study drug administration. Collect about 40 mg of liver tissue sample in one procedure of liver biopsy and a total of about 80 mg of tissue.

## 4.8 Amount of blood collected and the number of days of blood collection

The amount of blood collected from the subject on each visit is shown below.

As the laboratory test facility switches to a different method of HCV-RNA test (quantitative), the amount of blood collected will increase from 34 mL to 39 mL beginning in August 2008 for the days of evaluation on Week 48 and Week 96 of study drug administration.

|  | Amount of blood collected per day (ml) | Number of days of blood collection |
| --- | --- | --- |
| At the time of registration | 12 | 1 |
| Day of the start of administration | 39 | 1 |
| Day of evaluation at Week 8 of administration | 39 | 1 |
| Days of evaluation at Weeks 12, 36, 60 and 84 of administration | 18 | 4 |
| Days of evaluation at Weeks 24 and 72 of administration | 24 | 2 |
| Days of evaluation at Weeks 48 and 96 of administration | 39 | 2 |
| Days of evaluation at Weeks 4, 16, 20, 28, 32, 40, 44, 52, 56, 64, 68, 76, 80, 88 and 92 of administration | 14 | 15 |
| At the time of follow-up examination (Week 12 after completion of administration) | 22 | 1 |
| Total | 520 | 27 |

This table does not include any blood samples collected at the discretion of the investigator or the subinvestigator due to the occurrence of adverse events, etc.

## 4.9 Amount of urine collected and frequency of urine sample collection

Urine sample will be accumulated for 24 hours at the time of “4.7 Liver tissues collection (during hospitalization for liver biopsy),” on the day of evaluation at Week 48, on the day of evaluation at Week 96, and in the presence of increased blood pressure (if possible).

# 5. Criteria for inclusion and exclusion of subjects

Before selecting the subjects, the investigator, among others, will carefully evaluate patients for their fitness to participate in the study, with consideration given to the condition of health, age, gender, ability to give consent, depending relationship with the investigator, etc., and participation in other clinical studies so as to comply with human rights protection and the study objectives.

## 5.1 Study subject population

Subjects are patients who have undergone topical medical therapy or surgical resection after a diagnosis of HCV-positive HCC and have been confirmed to have achieved a complete cure from HCC.

[Rationale]

In Japan, 15.5% and 71.8% of the patients with HCC are believed to be positive for HBs antigen and HCV antibody, respectively.3) Moreover, the cumulative incidence rate of HCV-positive HCC is much higher than that of HCC induced by HBV or alcohol,23) and the risk of recurrence is also high. Furthermore, in some cases of HBV-positive HCC, HCC may develop in the early stage of hepatitis without progression from chronic hepatitis to liver cirrhosis. Therefore, unlike HCV-positive HCC, the process of carcinogenesis of HBV positive HCC is not uniform, and other factors may be involved. In light of these facts, the patients with a complete cure from HCV-positive HCC were considered appropriate as the subjects to be analyzed for evaluation of the study drug’s efficacy, which is “the effect to inhibit recurrent HCC,” considering the number of patients, risk of recurrence, and uniformity of the process of carcinogenesis in the phase II/III study of NIK-333. In this clinical pharmacology study, the same patients as those in the phase II/III study of NIK-333 were selected as the subjects for the analysis of the gene expression profile, with the aim of identifying the drug response gene for NIK-333.

## 5.2 Inclusion criteria

Select patients who meet the following criteria as the subjects.

[1] Patients with HCV-positive HCC who meet the following conditions before radical treatment

1) Patients diagnosed as having typical HCC on dynamic CT (MD) or CTA/CTAP

2) Patients with first primary HCC or the first recurrence of primary HCC (recurrence after an interval of at least one year after treatment of the first primary HCC)

[2] Patients who received one of the following treatments

1) Topical medical therapy

Patients who have undergone local radical therapy of HCC mainly by radiofrequency ablation (RFA). (However, percutaneous ethanol injection (PEI) or percutaneous microwave coagulation therapy (PMC) in combination with RFA are allowed.)

2) Surgical resection

Patients who have undergone liver resection

[3] Patients in whom complete cure has been confirmed by the following methods

1) Topical medical therapy

The dynamic CT images taken from 8 weeks (56 days) to 12 weeks (84 days) after topical medical therapy show no findings suggestive of recurrence at the treatment site and other sites, and the investigator or the subinvestigator has confirmed complete cure

2) Surgical resection

The dynamic CT images taken from 8 weeks (56 days) to 12 weeks (84 days) after liver resection show no findings suggestive of recurrence or residue, and the investigator or the subinvestigator has confirmed complete cure

[4] Patients who are able to begin treatment with the study drug within 8 weeks (56 days) after the dynamic CT to confirm complete cure

[5] Patients confirmed of satisfying the following conditions based on the screening performed at subject registration

1) HCV-RNA is present in serum.

2) Grade A or B on Child-Pugh classification 24.25)

| Score | | 1 | 2 | 3 |
| --- | --- | --- | --- | --- |
| liver encephalopathy | | None | Mild | Occasional coma |
| Ascites | | None | Small amount | Moderate amount |
| Serum bilirubin (mg/dL) | Patients other than those mentioned below | <2 | 2-3 | 3< |
| Patients with biliary cirrhosis primary | <4 | 4-10 | 10< |
| Serum albumin (g/dL) | | 3.5< | 2.8-3.5 | <2.8 |
| Prothrombin (s: seconds), (%: activity value) | | <4，70%< | 4-6，40-70% | 6<，<40% |

Grade A:5-6 points Grade B: 7-9 points Grade C: 10-15 points

3) Platelet count of 50,000/µL or higher

[6] Patients of the age of 20 years or older at the time of informed consent

[Rationale]

[1]: The patients with HCV-positive HCC of the first onset or first recurrence are deemed less likely to have intrahepatic metastasis than those who have repeated recurrences and were judged to be appropriate for confirming efficacy of the study drug (effect to inhibit recurrent HCC) in the phase II/III studies of NIK-333. In this clinical pharmacology study, the same patients will be selected as the subjects.

[3]: To improve the accuracy of confirmation of complete cure by evaluation of images and to exclude local recurrence (residue) as much as possible

[4]: It was considered necessary to start administration of the study drug within a certain period after confirmation of complete cure.

[5]: 2) and 3): To exclude patients with a severe condition in terms of the remaining liver functions.

[6]: To make it essential to obtain informed consent from the patient personally, or from the patient personally and his or her representative

## 5.3 Exclusion criteria

Patients who fall under any of the following criteria will be excluded.

[1] Patients positive for HBs antigen

[2] Patients showing portal infiltration of HCC on CT images

[3] Patients who have also undergone transcatheter arterial embolization therapy (TAE/TACE) as combination with the radical therapy

[4] Patients who have received other study drugs, anticancer drugs, interferons, or vitamin K2 after radical therapy

[5] Patients who have hypertension as a complication, and whose blood pressure cannot be controlled by drug therapy (systolic blood pressure of 160 mmHg or higher or diastolic blood pressure of 100 mmHg or higher, as determined at subject registration)

[6] Patients who have a history of allergy to CT contrast media, and whose participation in this study is judged to be inappropriate by the investigator or the subinvestigator

[7] Patients whose hemoglobin content is less than 8.0 g/dL and whose prothrombin time (%: activity value) is less than 40%, patients who are taking drugs with a potential of inducing blood coagulation abnormality, and patients who are judged to be ineligible for liver biopsy by the investigator or the subinvestigator

[8] Patients with a history of total gastrectomy

[9] Patients with serious complications (serious renal disorder, heart disease, diabetes mellitus, autoimmune disease, asthma, etc.)

[10] Patients confirmed of having another malignant neoplasm or who had undergone a radical therapy within the last 5 years to treat another malignant neoplasm (however, this does not apply to endoscopic resection and resection of intraepithelial carcinoma）

[11] Patients who are pregnant, who have a possibility of being pregnant or who have a desire to become pregnant during the study period

[12] Lactating women

[13] Patients who have a history of allergy to retinoid-related substances (vitamin A, etc.) in the past

[14] Other patients deemed ineligible to participate in the study by the investigator or the subinvestigator

[Rationale]

[1]: The subjects of the ongoing phase II/III study of NIK-333 are patients with HCV-positive HCC. Moreover, while the liver gene expression profiles reportedly are different between patients with HBV-positive hepatitis and patients with HCV-positive hepatitis, the virological background of the patients should be made uniform.

[2]: Because NIK-333 is not indicated for highly malignant HCC associated with portal infiltration

[3]: To avoid the use of anticancer drugs in transcatheter arterial embolization therapy (TAE/TACE)

[5]: To ensure safety of subjects in light of the fact that obvious increase of blood pressure was observed in the group treated with 900 mg in the phase I studies

[7]: To ensure the subjects’ safety during liver biopsy

[8]: Because absorption of NIK-333 may be affected

[11]: Because NIK-333 was confirmed to have teratogenicity and to induce miscarriage in the reproductive and developmental toxicity study

[12]: Because safety for fetuses has not been confirmed

[4]，[6]，[9]，[10]，[13]，[14]: To ensure the subjects’ safety and to eliminate any factors interfering with evaluation of the safety of the study drug

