| Cheilitis | 0 | 2 | 6 | 8 | 4.4 |
| Dry lip | 0 | 0 | 4 | 4 | 2.2 |
| Itching | 0 | 0 | 3 | 3 | 1.6 |
| Folliculitis | 0 | 1 | 0 | 1 | 0.5 |
| Plantar fissure | 0 | 0 | 1 | 1 | 0.5 |
| Nail fragility | 0 | 0 | 1 | 1 | 0.5 |
| Flickering feeling in the eyes | 0 | 0 | 1 | 1 | 0.5 |
| Itchy sensation of eyelids | 0 | 0 | 1 | 1 | 0.5 |
| Foreign body feeling of oesophagus | 0 | 0 | 1 | 1 | 0.5 |
| Stomach discomfort | 0 | 0 | 1 | 1 | 0.5 |
| Diarrhoea | 0 | 0 | 1 | 1 | 0.5 |
| Queasy | 0 | 0 | 1 | 1 | 0.5 |
| Burning sensation in face | 0 | 1 | 0 | 1 | 0.5 |
| Malaise in whole body | 0 | 1 | 0 | 1 | 0.5 |

Abnormal laboratory test values in a clinical study in patients with skin diseases 12)

| Parameter | Total number of events | Frequency (%) |
| --- | --- | --- |
| Transient increase of TG | 2 | 1.1 |

(2) Potential risks in this study

In this study, liver biopsy will be performed for determination of the liver gene expression profile and drug concentrations. Risks of complications associated with liver biopsy such as haemorrhage (haemorrhage from the liver surface at the puncture site), infection, pneumothorax (it can be induced if the lung is injured during the puncturing process), and shock (it can be caused by incompatibility with anesthesia) cannot be completely ruled out, although the likelihood is extremely small. Therefore, the operation should be performed with measures of precaution, including careful preliminary examination.

(3) Benefits for subjects

In non-clinical studies, oral administration of the doses of 40 mg/kg or more significantly inhibited hepatocarcinogenesis in rats induced by 3'-MeDAB and DEN15).

Muto et al. reported that in their clinical study of E-5166, a substance identical to NIK-333, a daily dose of 600 mg administered for 1 year to patients who received treatment for primary HCC significantly inhibited recurrent HCC, as compared with the placebo group,13) and improved the survival rate.14)

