# 7. Examination and observation parameters

## 7.1 Procedures of subject registration

(1) Informed consent and definite diagnosis

[1] Informed consent from the subjects

The investigator or the subinvestigator will evaluate patients who have undergone topical medical therapy or surgical resection, and obtain informed consent in writing from those patients deemed eligible to participate in this study.

[2] Confirmation of eligibility of the subjects

After an informed consent has been obtained from a subject, the investigator or the subinvestigator will perform the scheduled dynamic CT and various tests to confirm complete cure within 56 days before registration, and will confirm that the subject satisfies the inclusion criteria and does not fall under any exclusion criteria.

[Test parameters regarding the inclusion criteria and exclusion criteria]

1） Dynamic CT images

2） Medical examination (symptoms/signs)

3） Blood pressure (dorsal position or sitting position)

4） Child Pugh classification

(Liver encephalopathy, ascites, serum bilirubin, serum albumin and prothrombin time)

5) HCV-RNA tests (quantitative)

6) HBs antigen tests (qualitative)

7） HCG tests (pregnant or not: premenopausal women only)

8） Hematology tests (platelet count, hemoglobin level)

(2) Subject registration

The investigator or the subinvestigator will enter necessary information on the subject registration form and will fax it to the subject registration center. The sponsor will confirm on the subject registration form received (Fax) that there are no problems in the eligibility of the subjects.

(3) Study drug assignment and start of study drug administration

The investigator or the subinvestigator will start administration of the study drug according to the assignment table prepared in advance.

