## 7.4 Gene expression profile

(1) Liver biopsy

Perform liver biopsy to collect liver tissue samples for determinations of the liver gene expression profile drug concentrations.

[1] Liver biopsy procedure

Perform liver biopsy after the absence of the risk of haemorrhage has been confirmed in advance by the blood coagulation test, etc. Under local anesthesia, needle biopsy is performed with the aid of ultrasonography using a Bard Monopty automatic biopsy needle (Max Core). The specification is as follows: depth of insertion; 22 mm, external diameter; 16 G, needle length; 160 mm. The upper limit for the amount of liver tissue samples to be collected per day for determination of the gene expression profile and drug concentrations in the liver will be 20 mg, respectively. The patients will remain at rest for a while after liver biopsy. They will be hospitalized on the days of examination.

[2] Timing of liver biopsy and the acceptable range

On the day before the start of study drug administration and on the day of evaluation at Week 8 after the start of administration (4 hours after administration)

- 4 hours after administration: ±30 minutes

If a deviation from the designated timing of sample collection is within the acceptable range, the sample will be deemed as collected at the designated timing.

If the investigator or the subinvestigator deems that liver biopsy cannot be performed on the designated day of evaluation at Week 8 due to the subject’s health condition, the liver biopsy can be postponed by up to 28 days. In such cases, the period of Step I [the period of administration of two doses, i.e., 300 mg/day (twice daily) and 600 mg/day (twice daily)] will be extended until completion of liver biopsy.

[Rationale for timing of liver biopsy]

The rationale for the timing of liver biopsy is described, as the rationale for selection of the administration period for determination of the gene expression profile, in the section of “Rationale” under “4.4.(3) Study drug administration period” for determination of the gene expression profile.

From the results of the phase I single administration study, the appropriate timing of liver biopsy on the day of evaluation at Week 8 of study drug administration was deemed to be 4 hours after administration, which is close to the time point of the Cmax of unchanged NIK-333.

(2) Determination of the gene expression profile in the liver

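### Exclusion [7] requires low haemoglobin and low prothrombin activity together, so either abnormality alone passes a limit meant to protect subjects at liver biopsy

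*Protocol*

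**What the plan says.** Protocol 5.3, exclusion [7], has three limbs. The first is numeric: "Patients whose hemoglobin content is less than 8.0 g/dL and whose prothrombin time (%: activity value) is less than 40" per cent. The second covers patients on drugs that may disturb coagulation. The third is "patients who are judged to be ineligible for liver biopsy by the investigator or the subinvestigator". The summary (IV (3)) words [7] in the same way. The rationale in 5.3 says that [7] serves the subjects' "safety during liver biopsy".

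Other places that bear on the same risk:

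- Section 2.4 (2) names bleeding among the hazards: "Risks of complications associated with liver biopsy such as haemorrhage (haemorrhage from the liver surface at the puncture site").
- Sections 4.7 and 7.4 call for two biopsies per subject, the day before dosing and at Week 8, with a 16 G needle.
- Section 7.4 (1) sets a condition on the procedure: "Perform liver biopsy after the absence of the risk of haemorrhage has been confirmed in advance by the blood coagulation test, etc".
- Section 5.2 [5] admits Child-Pugh Grades A and B and requires platelets of at least 50,000/µL.
- Section 7.1 lists the eligibility tests, among them prothrombin time (within Child-Pugh) and "Hematology tests (platelet count, hemoglobin level").

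**The concern.** Severe anaemia and severely reduced prothrombin activity are separate reasons for caution before a needle biopsy of the liver. The first leaves less reserve if the patient bleeds, and the second makes bleeding more likely. A limit written to protect subjects at biopsy would be expected to act on either. As worded, it acts only when both are present.

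The biopsies are taken to obtain study samples for gene expression and drug concentration. If the only stated haemoglobin and prothrombin limits do not act on a single abnormal value, the decision on such a patient passes to controls that have no number attached.

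There is also a consequence for the analysis. Section 12.7 (1) takes the primary gene expression results from the PPS and removes subjects who violate the exclusion criteria from it. Whether a subject with one low value counts as a violator depends on this conjunction. With 6 subjects per group, one subject is 1/6 = 17% of an arm.

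**Working it through.** The plan gives no figure to reproduce. The check has three parts: reading the sentence, listing what it excludes, and testing whether another criterion covers what it misses.

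**1. Reading the sentence.** One noun governs both *whose* clauses in the numeric limb, so both must be true. The next two limbs each start again with the noun, which marks them as alternatives. The rest of the list in 5.3 follows the same usage:

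| Item | Construction | Meaning |
|---|---|---|
| [5] hypertension, uncontrolled on drugs | *and whose* | both needed |
| [6] contrast allergy, participation judged inappropriate | *and whose* | both needed |
| [5] "systolic blood pressure of 160 mmHg or higher or diastolic blood pressure of 100 mmHg or higher" | *or* | either suffices |
| [10] the two malignancy clauses | *or* | either suffices |
| [11] the three pregnancy clauses | *or* | any suffices |
| [7] haemoglobin, prothrombin | *and whose* | both needed |

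The opening line of 5.3, under which any one criterion excludes, works between criteria. It does not split the *and* inside [7].

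**2. What the numeric limb excludes.** Two conditions give 2 × 2 = 4 patterns:

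| Hb < 8.0 g/dL | Prothrombin < 40% | Excluded as written (*and*) | Excluded with *or* |
|---|---|---|---|
| no | no | no | no |
| no | yes | no | yes |
| yes | no | no | yes |
| yes | yes | yes | yes |

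Three patterns include at least one low value. As written, the limb excludes 1 of the 3; with *or*, it excludes all 3. These are patterns, not proportions of patients.

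**3. Whether another criterion closes the gap.**

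*Prothrombin.* The table in 5.2 gives 3 points for activity below 40%, and the grades are "Grade A:5-6 points Grade B: 7-9 points Grade C: 10-15 points". Each of the other four items scores 1 to 3.

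- Lowest total: 3 + (4 × 1) = 7, which is Grade B and eligible.
- Highest eligible total: 9, so the other four items may sum to at most 9 − 3 = 6.
- Eligible totals: 3 + 4 = 7, 3 + 5 = 8 and 3 + 6 = 9, that is, every Grade B total.
- Of the 3⁴ = 81 score combinations for the other four items, 1 + 4 + 10 = 15 (sums of 4, 5 and 6) remain eligible.

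*Haemoglobin.* No other criterion in 5.2 or 5.3 sets a limit. The platelet limit covers neither value.

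**The case against.** The strongest reply is that a patient with one low value does not go automatically to biopsy. Section 7.4 makes confirmed absence of haemorrhage risk a condition of the procedure. Prothrombin is a coagulation measure, and activity below 40% is the worst Child-Pugh band, so it is hard to reconcile with that condition. The condition also applies at both biopsies, whereas [7] is applied once, at registration. For haemoglobin, the investigator has the value at registration and again within 14 days before dosing, and can exclude under the last limb of [7] or under [14]. The wording may also be a translation slip, since the final *and* in [7] plainly joins alternatives.

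Much of this stands. The mitigation is real, and it is stronger for prothrombin than for haemoglobin. What does not follow is that the numeric limb can stay as it is. Neither the 7.4 condition nor the investigator's judgement has a threshold. The 7.4 condition names only coagulation testing and an open-ended *etc.*, so isolated low haemoglobin rests mainly on judgement. The plan chose to set numbers in addition to judgement, and those numbers should work. The final *and* joins limbs that each restate the noun; the numeric limb does not. A translation slip is possible, but this is the only text at hand and both places read the same.

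It could also be said that no analysis is touched. That is not so, because the PPS definition in 12.7 refers to the exclusion criteria.

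**Conclusion.** The concern holds. As worded in 5.3 and in the summary, the numeric limb of [7] does not exclude a patient with only one of the two abnormalities, which is contrary to its stated purpose. It catches one of the three abnormal patterns, and Child-Pugh admits prothrombin activity below 40% at every Grade B total (7, 8 and 9).

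The size in patients is unknown: the documents give no frequency for either abnormality, and the planned sample is 12. The practical risk is reduced by the pre-biopsy check, the platelet limit, the coagulation-drug limb and the investigator's judgement. The larger remaining gap is isolated low haemoglobin. The conclusion rests on the literal English text and takes the limits of 8.0 g/dL and 40% as intended. It is a criterion that should be corrected, and the correction is simple.

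**What to change.** In 5.3 [7] and in the summary (IV (3) [7]), exclude patients with haemoglobin below 8.0 g/dL *or* prothrombin activity below 40%, or list the two as separate items that each exclude alone. The clinical team should confirm both limits when making the change.

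The cost is rewording in two places. Both values are already obtained at registration under 7.1, so no test is added. A few more patients may be excluded at screening. The change acts at registration only; if the same limits are wanted before the Week 8 biopsy, they would also have to be written into the procedure in 7.4 (1).
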